### Other general measures

In both groups, a standardised neurological examination is performed every 4 h by the physicians and nurses in charge of the patient (GOS score, pupillary reflex, corneal reflex, cough reflex, spontaneous breathing, abnormal movements, focal neurological signs). Core body temperature is monitored continuously using an oesophageal probe and recorded every 4 h during the first 48 h after randomisation.

Patients are routinely screened for propofol infusion syndrome via measurements of arterial blood gas, serum lactate, serum triglycerides, and serum creatine phosphokinase every 8 h during the first 48 h after randomisation.

The prevention of secondary brain injury relies on temperature control to avoid hyperthermia in the control group and, after rewarming, in the therapeutic hypothermia group; glucose control between 0.8 and 1.4 g/L, maintenance of normoxia with PaO_2_ ≥ 80 mmHg and SaO_2_ ≥ 95 %; maintenance of normocapnia with PCO_2_ between 35 and 40 mmHg; 45° head-of-bed elevation; maintenance of mean arterial pressure between 70 and 90 mmHg; and serum sodium control between 138 and 142 mmol/L. Special attention is paid to the occurrence of aspiration pneumonia, and three samples for blood cultures are taken routinely within 24 h after randomisation.

### Safety and potential risks associated with the study

Rigorous monitoring procedures are implemented to minimise the risks associated with therapeutic hypothermia in patients after CSE. Continuous EEG monitoring is performed for 48 h after inclusion, and a 30-min EEG extract is interpreted centrally before implementation of the randomly allocated treatments. Although neuromuscular blockade can theoretically mask recurrent seizure activity, this risk is lessened by the anticonvulsant properties of therapeutic hypothermia.

Preliminary data show that 82 % of patients admitted to the ICU for CSE receive mechanical ventilation for longer than 24 h, and that nearly 25 % of those given mechanical ventilation for less than 24 h have a 90-day GOS score lower than 5. Thus, the use of mechanical ventilation for an unnecessarily long period seems very rare. No criteria are available for predicting which patients will require mechanical ventilation for less than 24 h. Finally, this study includes only patients with severe CSE requiring both ICU admission and mechanical ventilation.

Patients receiving therapeutic hypothermia and/or propofol are closely monitored for adverse effects of these treatments such as infections and propofol infusion syndrome. We therefore believe that the use of therapeutic hypothermia does not expose the patients to undue risks, given the high morbidity and mortality rate in our prospective study [4] and the safety measures included in the HYBERNATUS trial protocol.

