### Standardised anticonvulsant treatments after randomisation in both groups

To be eligible, patients should have received at least one of the first-line anticonvulsant drugs (clonazepam and diazepam) listed in French guidelines. Patients with ongoing motor seizures who have not received a second-line anticonvulsant (fosphenytoin, phenytoin, phenobarbital, or sodium valproate) before randomisation receive a loading dose of one of these drugs selected according to the indications and specific contraindications of each [33].

Patients with refractory CSE, defined as CSE persisting despite two lines of anticonvulsant therapy within 60 min, are given an intravenous 2 mg/kg propofol bolus followed by an additional intravenous 1 mg/kg bolus every 5 min until motor seizures stop, at which point a continuous intravenous propofol infusion is started at a rate of 2–5 mg/kg/h. In patients with uncontrolled refractory CSE despite continuous intravenous propofol at a rate of 5 mg/kg/h, anaesthetic drugs (midazolam or thiopental) can be added.

CSE must be controlled within 60 min after randomisation in both groups and before the induction of therapeutic hypothermia in the experimental group.

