### Therapeutic hypothermia group

The objective is to lower the core body temperature to 32–34 °C rapidly after randomisation and then to maintain this temperature for 24 h. The management in the therapeutic hypothermia group will include the following:sedation with propofol in a 1–2 mg/kg bolus followed by a maintenance infusion at a rate of 2–5 mg/kg/h; patients with refractory CSE before randomisation receive the propofol infusion rate that was required to stop the motor seizures;neuromuscular blockade with a 0.15 mg/kg bolus of cisatracurium or of another neuromuscular blocker followed by doses at 4-h intervals adjusted to maintain the response to train-of-four stimulation at two of four twitches;hypothermia induction with ice-cold intravenous fluids at 4 °C and then hypothermia maintenance with ice packs at the groin and neck and a cold-air tunnel around the patient’s body;after 24 h of hypothermia, passive rewarming by covering the patient with a warm blanket, at a slow rate of 0.25–0.5 °C per hour to avoid haemodynamic instability, cisatracurium is discontinued when normothermia is achieved; when the train-of-four response is four twitches, the propofol is stopped or decreased to the lowest dose needed to ensure tolerance of the endotracheal tube;If continued sedation is required, the choice of the sedative is at the discretion of the bedside physician, but propofol is not used for longer than 48 h;Core body temperature is monitored using an oesophageal probe throughout the therapeutic hypothermia phase and then during rewarming until two values 4 h apart are between 37° and 38° C.

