### Control group

The bedside physician decides whether sedation should be initiated and maintained. If sedation is given, the same propofol regimen as in the therapeutic hypothermia group is used (1–2 mg/kg bolus and then 2–5 mg/kg/h intravenous infusion rate). If sedation is inadequate with continuous intravenous propofol 5 mg/kg/h, benzodiazepines may be added. Finally, if sedation must be maintained beyond 48 h, the propofol must be stopped and an anaesthetic selected by the bedside physician given instead.

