### General management of convulsive status epilepticus (CSE) in both groups

In both control and intervention groups, a continuous EEG monitoring is started within 2 h after randomisation and maintained during the first 48 h after randomisation and/or until body temperature normalisation in the therapeutic hypothermia group. A 30-min standard EEG extracted from the continuous EEG recording is sent for centralised interpretation by a qualified neurophysiologist within 2 h after the initiation of continuous EEG monitoring. If the results show refractory CSE or progression to NCSE, the patient is given a 2-mg/kg propofol bolus, repeated every 5 min if necessary, and then a maintenance intravenous infusion at 2–5 mg/kg/h to obtain and maintain a burst-suppression EEG pattern for 24 h. Further EEG epochs are sent for centralised interpretation by a qualified neurophysiologist until a burst-suppression EEG pattern is observed.

Second-line anticonvulsant drugs administered intravenously are switched to enteral administration when feasible. Patients with a known history of epilepsy are given their previous treatment enterally or parenterally. Aetiological investigations are carried out early, simultaneously with the symptomatic and anticonvulsant treatment. They include a thorough initial physical examination and tests for metabolic disturbances (e.g. hypoglycaemia, hypocalcaemia, hyponatraemia, uraemia, hypomagnesaemia, hypoxaemia, and hypercapnia) and carbon monoxide poisoning. Computed tomography (CT) of the brain is performed routinely. In patients with previously treated epilepsy, serum anticonvulsant drug assays are performed if appropriate, to determine whether levels are within the therapeutic range. As dictated by the clinical setting, tests are performed for disorders such as porphyria and thyroid dysfunction and/or for toxic substances (alcohol, cocaine, amphetamines, tricyclic, or serotonergic antidepressants). A lumbar puncture is performed in patients with any of the following: fever, meningeal neck stiffness, immunodeficiency, and negative findings from the other aetiological investigations. Magnetic resonance imaging (MRI) may be considered if all other aetiological investigations are negative [34].

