#### Secondary outcomes

Secondary outcomes are as follows:Percentages of patients with recurrent convulsive and/or non-convulsive seizures between 6 and 12 h after randomisationTotal seizure duration in minutesPercentage of patients with refractory status epilepticusMortality in the ICU, in the hospital, and by day 90Total ICU and hospital stay lengths in daysPercentages of patients with functional impairments on day 90: frequency of seizures, recurrence of status epilepticus after discharge, number of antiepileptic drugs, MMSE score, and FIM score

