#### Secondary outcomes

The method described above for the primary outcome will also be used for the percentages of patients with EEG evidence of an ongoing epileptic seizure between 6 and 12 h or of refractory SE after randomisation; ICU, hospital, and 90-day mortality; and 90-day functional impairments.

To compare seizure duration (in minutes), we will build a semi-parametric regression model (Cox or Fine–Gray) appropriate for an analysis of competing risks (control of SE vs. death without control of SE). This approach will be used also for ICU and hospital stay lengths (alive at ICU or hospital discharge vs. death in the ICU or hospital, respectively).

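### The 6–12 h seizure outcome has two definitions, and the wider one could count seizures seen only clinically mainly in controls, because blockade is prescribed only in the hypothermia arm

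*Protocol article*

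**What the plan says.** The outcome list (Protocol article, Study outcomes, Secondary outcomes) gives the percentage of patients with "recurrent convulsive and/or non-convulsive seizures between 6 and 12 h after" randomisation, with no EEG requirement. The analysis text (Statistical methods, Secondary outcomes) applies the logistic regression method to the "percentages of patients with EEG evidence of an ongoing epileptic seizure between 6 and 12 h".

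In the Therapeutic hypothermia group section, a neuromuscular blocker is part of the regimen. It is re-dosed every 4 h to a target of two of four twitches, and "cisatracurium is discontinued when normothermia is achieved". The Control group section prescribes no blocker: "The bedside physician decides whether sedation should be initiated and maintained", and the rest of that section concerns sedatives.

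On detection, Other general measures states that "a standardised neurological examination is performed every 4 h by the physicians and nurses in charge of the patient", and abnormal movements are among the items checked. General management of CSE provides continuous EEG in both arms for the first 48 h. The safety section names that EEG monitoring and then adds: "Although neuromuscular blockade can theoretically mask recurrent seizure activity, this risk is lessened by the anticonvulsant properties of therapeutic hypothermia".

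**The concern.** The two definitions differ on one kind of event: a seizure recognised at the bedside and not confirmed on EEG. It counts under the outcome list and not under the analysis text. In many trials that would be a harmless difference of wording. Here the arms differ in how visible such an event is. Controls can show motor signs, whereas in the hypothermia arm blockade can hide them.

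This outcome bears directly on the secondary aim of seizure control. The protocol requires that "CSE must be controlled within 60 min after randomisation in both groups and before the induction of therapeutic hypothermia", so seizures recurring at 6–12 h arise after cooling should have begun. If the wider definition were used, an apparent anticonvulsant benefit could come from unequal detection.

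The safety section's reply does not settle this. Even if hypothermia lowers the number of seizures, it does not make the remaining ones easier to see. The Background also says that proof of a beneficial effect in human patients has not been obtained.

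**Working it through.** **Plan's own figure.** The document gives no event rate or power for this outcome. The only figure borrowed is 135 per group, from Sample size. For the primary outcome (40% v 60%, two-sided 5%, 90% power), the pooled two-proportion formula gives 130 per arm, or 140 with continuity correction. Power at 135 is 91.2%. The stated size is reasonable, and this point does not depend on it.

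**Does blockade cover the window?**
- Latest documented start of cooling: EEG begins within 2 h of randomisation, and the first extract "is sent for centralised interpretation by a qualified neurophysiologist within 2 h after the initiation of continuous EEG monitoring". The safety section has it read before allocated treatment starts. So 2 + 2 = about hour 4.
- Earliest stop of the blocker: even if cooling to 34 °C were immediate at hour 0, there follow 24 h of hypothermia, then rewarming at no more than 0.5 °C/h to 37 °C (taken as normothermia). 24 + (37 − 34)/0.5 = hour 30.
- For any start up to hour 6, blockade therefore spans all 6 h of the 6–12 h window.

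**How large could the bias be?** Let p be the true event rate, equal in both arms, and c the share of seizures seen clinically but missed on EEG. Under the wider definition the observed rates are p in controls and p(1 − c) with hypothermia. A false benefit is declared when z = (p̂_C − p̂_H)/√(2p̄(1 − p̄)/135) > 1.96. Its probability is summed exactly over the two binomial distributions, n = 135 per arm. This simple test stands in for the planned logistic regression.

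Example with p = 20% and c = 10%: expected counts are 135 × 0.20 = 27.0 and 135 × 0.18 = 24.3. The apparent odds ratio is (0.18/0.82)/(0.20/0.80) = 0.88.

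Probability of a false benefit:

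| Clinical-only share c | p = 10% | p = 20% | p = 30% |
|---|---|---|---|
| 0 | 2.5% | 2.5% | 2.5% |
| 2% | 2.9% | 3.1% | 3.2% |
| 5% | 3.5% | 4.0% | 4.6% |
| 10% | 4.7% | 6.2% | 8.0% |
| 20% | 8.3% | 13.5% | 20.0% |
| 30% | 14.1% | 25.9% | 40.0% |

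Both p and c are assumptions. The model also takes it that no control is paralysed and that no seizure is detected clinically under blockade, so each entry is an upper reading for its c. Under the EEG definition, seizures seen only clinically count in neither arm, so this source of bias is zero.

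**The case against.** The strongest reply is that the analysis text already uses the EEG definition, and it is the only place that says how this outcome will be analysed. The two sections can even be read together, one naming the seizure types and the other the means of detection. This stands as a limit on the concern: a reader might infer that the planned analysis is biased, and the document does not support that. The outcome list still carries a definition that admits events the analysis excludes.

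A reader might also infer that masking is left without a safeguard. That is not supported either. Continuous EEG runs in both arms, and the safety section names it just before the quoted sentence. A masked convulsion recorded on EEG counts under either definition. The quoted sentence is a patient-safety argument and claims only that the risk is lessened.

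Blockade is partial, and nothing forbids it in controls, so it would be too strong to say that motor signs are abolished in one arm only. Nothing in the document supports a clinical-only share as high as 10–30%, given EEG running throughout; at 2–5% the inflation is small. The missing clock times for EEG extracts and the unstated blinding of EEG readers are details an article may leave to the full protocol, and they are not part of this point.

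Lastly, propofol is prescribed with hypothermia but sedation is discretionary in controls, and the Discussion credits propofol with anticonvulsant effects. A cleaner definition will not by itself isolate the effect of cooling. That is true, but it is no reason to keep two definitions.

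**Conclusion.** The inconsistency is real and worth correcting before the analysis is run. It matters because blockade makes clinical detection unequal across the whole window. At an assumed 20% event rate with 135 per arm, the wider definition would raise the chance of a false benefit from 2.5% to about 3–4% if 2–5% of seizures were seen only clinically, and to 6–26% if 10–30% were. The excess is zero if EEG catches every seizure or if the EEG definition is applied. These are ranges on assumed inputs, not estimates of what happened in the trial.

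The point is confined to this secondary outcome. The primary outcome, the day-90 Glasgow Outcome Scale score by blinded phone interview, is unaffected.

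**What to change.** Before analysis, bring the outcome list into line with the statistical methods: count a patient only if a seizure between 6 and 12 h is confirmed on EEG, by the same rule in both arms. Report clinically observed convulsions in that window separately by arm, as description, with a note that blockade can mask motor signs in the hypothermia arm. In the safety section, rest the answer to masking on continuous EEG and drop the appeal to hypothermia's anticonvulsant effect.

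This needs no new patient data and no additional central EEG reading. Trial status reports that enrolment is complete and the analysis still ongoing, and the protocol already provides for justifying changes to the analysis plan in the final report.

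The cost is that genuine seizures seen only clinically drop out of the count. At a 20% rate (27 expected events per arm), a 2–5% share is 27 × 0.02 = 0.5 to 27 × 0.05 = 1.4 events in the control arm. At a 10–30% share it would be 2.7 to 8.1. The separate descriptive report keeps those events visible.

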### Data collection and follow-up

The following baseline characteristics are recorded at admission: age, sex, date and time of ICU admission, McCabe score and Knaus score, and pre-existing comorbidities. The Simplified Acute Physiology Score II is computed 24 h after ICU admission.

The study protocol also requires collection of the following data:Description of the CSE: circumstances of onset, date and time of onset and of seizure control, clinical features of seizures, pre-hospital and hospital providers and timing of anticonvulsant and supportive treatments, results of aetiological investigations (brain CT, lumbar puncture, MRI, laboratory tests including toxicological screen), aetiological diagnosis, type and dosage of antiepileptic drugs, and date and start and stop times of continuous EEG monitoring;Data related to ICU and hospital management: description of the acute disease; description of organ failures according to the Logistic Organ Dysfunction score (at inclusion and on days 0, 1, 2, 7, 14, and 28); use of mechanical ventilation, inotropic support, and/or renal replacement therapy; vital and functional status at ICU and hospital discharge according to the GOS; and cause of death (treatment limitation decision, refractory SE, and/or ICU complications);Data related to therapeutic hypothermia: modalities of induction and maintenance; core temperature every 4 h during the first 48 h; serum levels of creatine phosphokinase, triglycerides, and electrolytes; arterial lactate and blood gas levels; electrocardiogram; occurrence of aspiration pneumonia; and results of blood cultures on samples taken within the first 24 h;Data related to outcomes: 90-day GOS score by structured phone interview and neurologist visit; description of functional sequelae; mini–mental state examination (MMSE) score; and Functional Independence Measure scale (FIM) score.

#### Coordination and conduct of the trial

Before recruitment of the first patient, all physicians and other healthcare workers in the 11 participating ICUs attended formal training sessions on the study protocol, data collection in the case-report form (CRF), and implementation of continuous EEG monitoring. All documents required for the study, including the study protocol and management guidelines, are available in each participating ICU. In each participating ICU, the physicians and a clinical research nurse and/or clinical research assistant are in charge of daily patient screening and inclusion, ensuring compliance with the study protocol, and collecting the study data in the CRF. Finally, all participating physicians are available for inclusion and continuous EEG monitoring around the clock and 7 days per week. The DRCD clinical research unit regularly reviews all clinical data collected in the CRF. Any serious adverse event must be reported within 48 h after its occurrence.

### Interim analyses

An interim analysis is scheduled after the enrolment of 135 patients. The O’Brien-Fleming method will be used.

### Blinding

Blinding of the physicians, nurses, and patients to the use of therapeutic hypothermia is not feasible. To minimise evaluation bias, outcomes will be evaluated during a structured phone interview by independent assessors blinded to the allocation group.

### Study outcomes

#### Primary outcome

The primary outcome is GOS score determined by a structured interview lower than 5 on day 90.

#### Secondary outcomes

Secondary outcomes are as follows:Percentages of patients with recurrent convulsive and/or non-convulsive seizures between 6 and 12 h after randomisationTotal seizure duration in minutesPercentage of patients with refractory status epilepticusMortality in the ICU, in the hospital, and by day 90Total ICU and hospital stay lengths in daysPercentages of patients with functional impairments on day 90: frequency of seizures, recurrence of status epilepticus after discharge, number of antiepileptic drugs, MMSE score, and FIM score

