**Fig. 2 Fig2:**
[figure not shown]
Eligibility criteria, inclusion, randomisation, and treatment implementation modalities in each arm of the trial

**Table 1 Tab1:** HYBERNATUS trial flow chart

	Inclusion	Day 0	Day 1	Day 2 Day 7 Day 14 Day 28	ICU discharge	Hospital discharge	Day 90 (±7 days)
Eligibility: check inclusion and non-inclusion criteria	X						
Patient/next of kin information and consent	X						
Randomisation (within 8 h after CSE onset)		X					
Standardised anticonvulsant treatment		X					
Brain imaging and other aetiological investigations		X					
Therapeutic hypothermia (in the intervention group)		X	X				
Core temperature monitoring (every 4 h)		X	X				
Continuous EEG monitoring		X	X				
30-min continuous EEG extract (centralised reading)		X	X				
Clinical and laboratory monitoring		X	X	X	X		
Serious adverse event reporting		X	X	X	X	X	X
Glasgow Outcome Scale (GOS) score evaluation					X	X	X^1, 2^
Standard EEG							X^2^
Brain MRI							X^2^
MMSE score							X^2^
FIM scale score							X^2^
Neurological evaluation							X^2^

^1^By phone interview in all cases

^2^Neurologist visit, if feasible

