### Modalities of outcome evaluation

The GOS score is determined on day 90 (±7 days) during a structured phone interview conducted by an independent assessor blinded to the allocation group (Table 2).

**Table 2 Tab2:** Categories of the Glasgow Outcome Scale Adapted from Jennett B et al.

Category	Classification	Description
1	Death	Patient is certified dead
2	Vegetative state	Patient is unable to interact with the environment *Patients who show no evidence of meaningful responsiveness. This non*-*sentient state must be distinguished from other conditions of wakeful, reduced responsiveness*–*such as the locked*-*in syndrome, akinetic mutism, and total global aphasia. Vegetative patients breathe spontaneously, have periods of spontaneous eye*-*opening, may follow moving objects with their eyes, show reflex responses in their limbs (to postural or painful stimuli), and they may swallow food placed in their mouths*
3	Severe disability	Patient is unable to live independently but can follow commands *This indicates that a patient is conscious but needs the assistance of another person for some activities of daily living every day. This may range from continuous total dependency to the need for assistance with only one activity*
4	Moderate disability	Patient is capable of living independently but unable to return to work or school *Such a patient is able to look after himself at home, to get out, and about to the shops and to travel by public transport. However, some previous activities, either at work or in social life, are now no longer possible by reason of either physical or mental deficit*
5	Mild or no disability	Patient is able to return to work or school *This indicates the capacity to resume normal occupational and social activities, although there may be minor physical or mental deficits. However, for various reasons, the patient may not have resumed all his previous activities and in particular may not be working*

When possible, on day 90 (±7 days), patients return to the centre where they were included, for an evaluation by a neurologist including an interview and determination of the GOS score by structured interview, MMSE score, and FIM score. The patient brings an MRI of the brain and conventional EEG. The neurologist records any recurrent CSE episodes since randomisation; frequency of any recurrent seizures, as well as their type and associated symptoms; nature and dosage of antiepileptic drugs; and other treatments.

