### Statistical methods

The statistical analysis will follow the intention-to-treat approach, with each patient being analysed as a member of the group assigned by randomisation, regardless of subsequent events. In addition, any missing value will be replaced by the previous value according to the last value carried forward method. A sensitivity analysis of missing values will be carried out, using multiple imputation by chained equations (MICE). Comparisons of the two groups will routinely consider a possible centre effect.

A statistical analysis report will be written to describe all the findings according to CONSORT statement recommendations, taking into account the specific features of the trial. Any change in the analysis plan will be justified in the final report.

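### Carrying the last value forward cannot supply day-90 MMSE or FIM and no value is set for deaths, so the functional comparison may rest on surviving attenders

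*Protocol article*

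**What the plan says.** - **Outcomes.** Study outcomes, Secondary outcomes, defines day-90 functional impairment as a set of percentages: "frequency of seizures, recurrence of status epilepticus after discharge", number of antiepileptic drugs, MMSE and FIM.
- **Collection.** Table 1 marks MMSE, FIM and the neurological evaluation at day 90 only, under the footnote "Neurologist visit, if feasible". The other footnote, "By phone interview in all cases", is attached to the GOS row alone. Modalities of outcome evaluation agrees: "When possible, on day 90 (±7 days), patients return to the centre where they were included, for an evaluation by a neurologist". The same section adds "The neurologist records any recurrent CSE episodes since randomisation; frequency of any recurrent seizures", together with antiepileptic drugs. The Blinding section, however, says in general terms that outcomes are assessed by blinded telephone interview.
- **Analysis.** Statistical methods, Secondary outcomes, applies the primary outcome's logistic regression to a list ending "ICU, hospital, and 90-day mortality; and 90-day functional impairments". Death is named as a competing event for seizure duration and lengths of stay. No value for death is given for the functional impairments.
- **Missing data.** Statistical methods sets intention to treat and says "any missing value will be replaced by the previous value". Multiple imputation by chained equations (MICE) is a sensitivity analysis.

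**The concern.** A carry-forward rule needs an earlier measurement of the same quantity. For MMSE and FIM none is scheduled, so the main rule cannot be carried out on the two graded outcomes. For drug number, the acute-phase record listed under Data collection and follow-up could be entered as the day-90 value, including for someone who has died. Neither the main rule nor the sensitivity analysis says what a dead patient's functional score means.

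If no usable value exists, the regression in practice runs on those who survived and could travel. Both conditions arise after randomisation and may depend on treatment, so the protection of randomisation is lost for these outcomes. A treatment that turns deaths into survival with disability could then look neutral or harmful on function, and the opposite could happen for a harmful treatment.

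**Working it through.** **The plan's own figure.** The article gives no figure for the functional outcomes. Its design figure, 135 per group, belongs to the primary outcome. The pooled two-proportion formula (40% vs 60%, two-sided 5%, 90% power) gives 129.3 per group. Multiplying by 1.0071 for one O'Brien-Fleming interim gives 130.2, so 131, which is close to 135. It has no bearing on this point.

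**Step 1: is there an earlier value to carry?**

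| Item | Earlier scheduled value | Effect of the rule |
|---|---|---|
| GOS | Yes: ICU and hospital discharge (Table 1) | Can be applied |
| MMSE, FIM | None (Table 1: day 90 only) | Cannot be applied |
| Number of drugs | Acute-phase type and dosage (Data collection) | Could enter an acute regimen as day 90 |

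**Step 2: patients without a score through death alone.** Background cites hospital mortality of about 20% overall and 40% in severe refractory CSE. 0.20 × 270 = 54; 0.40 × 270 = 108. Day-90 mortality in this ventilated population is not given, so this is a range and not a forecast.

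**Step 3: illustration.** From the article: 135 per arm, control GOS 5 of 40% (54 patients), mortality 20% (27 deaths). Assumed, because the article gives nothing: the other 54 controls are 27 severe and 27 moderate; the chance of being rated impaired is 0.95 / 0.50 / 0.10 and attendance is 0.3 / 0.7 / 0.8 (severe / moderate / good). Hypothermia averts 14 deaths, of which 10 become severe and 4 good, giving 13 dead, 37 severe, 27 moderate, 58 good.

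Impaired among attenders = Σ(n × attendance × impairment) / Σ(n × attendance):
- Control: (7.695 + 9.45 + 4.32) / (8.1 + 18.9 + 43.2) = 21.465 / 70.2 = 30.6%
- Hypothermia: (10.545 + 9.45 + 4.64) / (11.1 + 18.9 + 46.4) = 24.635 / 76.4 = 32.2%
- Odds ratio: (24.635 / 51.765) / (21.465 / 48.735) = 1.08

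All randomised, death counted as impaired = (deaths + Σ(n × impairment)) / 135:
- Control: (27 + 25.65 + 13.5 + 5.4) / 135 = 71.55 / 135 = 53.0%
- Hypothermia: (13 + 35.15 + 13.5 + 5.8) / 135 = 67.45 / 135 = 50.0%
- Odds ratio: (67.45 / 67.55) / (71.55 / 63.45) = 0.89

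**Step 4: vary the assumptions.**

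| Scenario | OR, attenders | OR, all randomised |
|---|---|---|
| 14 deaths averted, severe attendance 0.3 | 1.08 | 0.89 |
| Same, severe attendance 0 | 0.97 | 0.89 |
| Same, severe attendance 0.6 | 1.13 | 0.89 |
| Same, every survivor attends | 1.15 | 0.89 |
| Planned 40% to 60% effect spread proportionally (18 / 18 / 18 / 81) | 0.63 | 0.56 |
| Equal deaths (27 / 20 / 24 / 64) | 0.80 | 0.81 |

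The change of direction remains when every survivor attends, so in these scenarios it comes mainly from leaving out deaths. It is absent in the last two rows and when no severely disabled patient attends.

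**Step 5: sampling error.** Take control 20% dead, 40% impaired, 40% good, and hypothermia 10%, 50%, 40% (assumed). Among survivors, impairment is 0.40 / 0.80 = 50.0% vs 0.50 / 0.90 = 55.6%, while death or impairment is 60% in both arms. With 108 and 121.5 survivors, the standard error of the 5.6-point gap is √(0.25/108 + 0.247/121.5) ≈ 6.6 points, so z ≈ 0.8. The distortion is real in expectation but smaller than this trial's random error.

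**The case against.** A reader might infer that the plan excludes deaths and non-attenders. The text does not say so: it commits to intention to treat, gives a rule for every missing value, and plans MICE as a check. An analysis on attenders is a likely practical result of a rule with nothing to carry, not a stated intention.

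A reader might also infer that the functional comparison will reverse. Step 4 does not support that. Reversal needs a mortality difference and particular assumptions, and the planned effect spread proportionally does not produce it. The example in Step 5 is a departure from equality on death or impairment, not a reversal.

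Collection only at the visit is firm for MMSE and FIM. For seizures, recurrence and drugs it is less certain, because the Blinding section leaves room for telephone collection.

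Death remains visible in the three mortality outcomes and in the primary GOS, where it is category 1. Impairment cut-offs may sit in a statistical analysis plan that is not shown, so their absence is not raised here.

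All of this limits the point without removing it. The carry-forward rule is stated, is made to cover any missing value, and cannot be applied to MMSE and FIM.

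**Conclusion.** The point holds for the day-90 functional outcomes, which are secondary. It is firmest for MMSE and FIM, where the main missing-data rule has no input. For drug number the rule has an input of the wrong kind. For deaths neither the main rule nor the sensitivity analysis gives a meaningful value.

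The possible bias depends on a mortality difference between arms. Its size cannot be fixed from the article, which gives neither attendance nor impairment rates. The shift from 0.89 to 1.08 shows what can happen under assumed rates and is not an estimate. The primary comparison does not depend on this, since GOS includes death and is obtained by telephone for everyone.

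**What to change.** - For the day-90 functional outcomes, replace last value carried forward by multiple imputation as the main method for surviving non-attenders. Use the blinded telephone GOS, discharge GOS and the stratification factors (centre, age group, seizure duration) as predictors.
- Do not impute scores for patients who died. In the comparison of all randomised patients count death as unfavourable, in line with the primary GOS. Label any survivors-only result descriptive and show it beside mortality.
- Reconcile the Blinding section with Modalities of outcome evaluation on whether seizures, recurrence and drugs are collected by telephone, at the visit, or both.

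Trial status says enrolment is complete and analysis ongoing, so the change should be fixed before the group comparisons are seen. Statistical methods already provides for justified changes in the final report. The cost is wording and some extra analysis, using data already scheduled for collection. The composite is less direct to read than a percentage among survivors.
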